# STUDY PROCEDURES

## Screening

For screening procedures see the Schedule of Events and the Assessments Section. Screening activities may only begin after a subject has signed consent. Consent signing can occur electronically via REDCap. All screening activities must take place within ≤ 35 days prior to the first MBSR unless otherwise noted.

During screening, subjects will also be provided with a list of resources including reading materials and on-line resources if they would like to further investigate the topic of psilocybin-assisted psychotherapy. Consenting can be completed via paper or electronic forms. Participants will be administered the MBI-HSS(MP) and the PHQ-9 to evaluate eligibility for participation prior to consent. A waiver of consent will need to be obtained by the IRB to administer questionnaires prior to consenting.

## Randomization and study arm assignment

Participants who meet eligibility criteria and have consented and enrolled in the study will be randomized to either the MBSR Arm or the MBSR + PAP arm using a randomization plan generated by the SAS code, PROC plan. The study will be open label and participants will be informed as to study arm assignment prior to the first MBSR session. There will be rolling enrollment in trial participation up until the cut-off registration date prior to each MBSR course starting date. Each arm will be run independently given likely variation on numbers of participants willing to complete each study arm however efforts will be made to run both arms concurrently depending on recruitment. While the MBSR only arm can be completed on an individual basis for each participant the MBSR + PAP arm includes group-based psilocybin-assisted therapy interventions which requires 2-5 participants per MBSR cohort. We will leave open the option of running group PAP sessions for a cohort of only 2 participants however will have a goal participant number per cohort of 4 with the possibility of running up to 5 participants per cohort through this arm. To assess expectancy effects on treatment response participants will be administered expectancy scales prior to randomization to assess preference as well as post randomization to assess credibility.

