**Table 2: Schedule of Events**

| **Week** | **-5 to -1** | | **1** | **2** | **3** | **4** | **5** | **6** | **7** | **8** | **9** | **11** | **33** |
| --- | --- | --- | --- | --- | --- | --- | --- | --- | --- | --- | --- | --- | --- |
| **Day** | **-35 to -7** | | **0-7** | **8-14** | **15-21** | **Etc.** |  |  |  |  |  |  |  |
| **Study Stage** | **Screen** | | **Active** | | | | | | | | | **Follow-up^[[1]](#endnote-1)^** | |
| Informed consent, registration | x |  |  |  |  |  |  |  |  |  |  |  |  |
| Eligibility criteria | x |  |  |  |  |  |  |  |  |  |  |  |  |
| Demographics | x |  |  |  |  |  |  |  |  |  |  |  |  |
| Medical History | x |  |  |  |  |  |  |  |  |  |  |  |  |
| Vitals and PE^[[2]](#endnote-2)^ | x |  |  |  |  |  |  |  |  |  |  |  |  |
| Randomization/assignment | **x** |  |  |  |  |  |  |  |  |  |  |  |  |
| Expectancy Questionnaires |  | **x** | **x** |  |  |  |  |  |  |  |  |  |  |
| **MBSR ARM** |  |  | **1** | **2** | **3** | **4** | **5** | **6** | **7** | **8** | **9** | **11** | **33** |
| **MBSR course** |  |  | **x** | **x** | **x** | **x** | **x** | **x** | **x** | **x** |  |  |  |
| **Retreat** |  |  |  |  |  |  |  |  | **x** |  |  |  |  |
|  |  |  |  |  |  |  |  |  |  |  |  |  |  |
| **PAP-MBSR** |  |  | **1** | **2** | **3** | **4** | **5** | **6** | **7** | **8** | **9** | **11** | **33** |
| Comprehensive Metabolic Panel ^xi.^ |  | x |  |  |  |  |  |  |  |  |  |  |  |
| Urine drug screen |  | **x** |  |  |  |  |  | x (within 24 hrs) |  |  |  |  |  |
| Pregnancy test ^iii^ |  | x |  |  |  |  |  | x (within 8 days of PAP) |  |  |  |  |  |
| MBSR Course |  |  | **x** | **x** | **x** | **x** | **x** | x | x | **x** |  |  |  |
| Prep Sessions 1-3 |  |  |  |  |  |  | **x** | x |  |  |  |  |  |
| PAP Session |  |  |  |  |  |  |  |  | x |  |  |  |  |
| Vitals monitoring |  |  |  |  |  |  |  |  | **x^[[3]](#endnote-3)^** |  |  |  |  |
| Integration Sessions 1-3 |  |  |  |  |  |  |  |  | **x** | **x** | **x** |  |  |
| **Assessments** |  |  | **1^[[4]](#endnote-4)^** | **2** | **3** | **4** | **5** | **6** | **7** | **8^[[5]](#endnote-5)^** | **9** | **11** | **33** |
| PHQ-9 | x |  |  |  |  |  |  |  |  |  |  |  |  |
| MBI-HSS (MP) | x |  | x |  |  |  |  |  |  |  |  | x | **x** |
| QIDS-SR-16 |  |  | x |  |  |  |  |  |  |  |  | x | **x** |
| Demoralization II scale |  |  | x |  |  |  |  |  |  |  |  | x |  |
| PTSD Checklist 5 |  |  | x |  |  |  |  |  |  |  |  | x | **x** |
| MEQ-30 |  |  |  |  |  |  |  |  | x |  |  |  |  |

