| Challenging Experience Questionnaire |  |  |  |  |  |  |  |  | x |  |  |  |  |
| Nondual Awareness Dimensional Assessment (state) |  |  |  |  |  |  |  |  | x | **x** |  |  |  |
| Nondual Awareness Dimensional Assessment (trait) |  |  | **x** |  |  |  |  |  |  |  |  | **x** |  |
| Watts’ Connectedness Scale |  |  | x |  |  |  |  |  |  |  |  | x | **x** |
| Toronto Mindfulness Scale, FFMQ-15 |  |  | x |  |  |  |  |  |  |  |  | x | **x** |
| Brief Savoring Inventory |  |  | x |  |  |  |  |  |  |  |  | x |  |
| **Storyline Health Questionnaires** |  |  |  |  |  |  |  |  |  |  |  |  |  |
| **Storyline Integrative Assessment**: Neurological, Psychiatric, Cognitive, Psychological |  |  | x |  |  |  |  |  |  |  |  | x | **x** |
| Qualitative assessment on workplace functionality ^vii.^ |  |  | x |  |  |  |  |  |  |  |  | x |  |
| Qualitative assessment on relationship between mindfulness training and psilocybin session and group format ^x^ |  |  |  |  |  |  |  | **x** |  |  |  | x |  |
| **Safety** |  |  |  |  |  |  |  |  |  |  |  |  |  |
| CTCAE Adverse Event collection^[[6]](#endnote-6)^ | x |  | x |  | x |  | x | x | x | x | x | x | **x** |
| Assess suicidality: C-SSRS ^x^ | x |  |  |  |  |  |  | x |  | x | x | **x** | **x** |
| Assess concomitant meds | x |  | x |  | x |  | x | x | x | x | x | x | **x** |

^i.^ Follow up measures to be administered 14 days (+/- 3) and 180 days (+/-7) after final MBSR session in week 8.

^ii.^ Vital signs include systolic and diastolic blood pressure, heart rate, respiratory rate, pulse oximetry, weight. Weight captured at screening only.

^iii.^ Pregnancy test (serum or urine) must be obtained at screening and ≤ 8 days prior to psilocybin administration for all women of childbearing potential and as clinically indicated while on trial.

^iv.^ On day of psilocybin administration vital signs will be assessed approx. 10 min before dosing and at 30, 50, 90, 120, 180, 240, 300, and 360 minutes after psilocybin administration. The baseline vitals will be allowed a 60-minute window to collect prior to dosing, while each subsequent vital collection will be allowed a window of +/- 15 minutes.

^v.^ All Questionnaires scheduled for MBSR Week 1 to be administered prior to the first MBSR session. Questionnaires and safety measures assessed similarly across both study arms.

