## Laboratory Assessments

Samples for all laboratory assessments will be drawn at the time points indicated in the Schedule of Events and when clinically indicated. All safety laboratory analyses will be performed by the local laboratory. All safety laboratory assessments must be reviewed by the treating investigator prior to study drug administration. When applicable, results from the pregnancy test must also be available for review prior to dosing. Laboratory screening will only be required for participants randomized to the MBSR + PAP arm to ensure safe and effective administration of study drug.

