## Statistical Analyses

Aim 1 is to assess the safety and feasibility of MSBR and PAP for burnout. We will track frequency and percentage of adverse events and rates of serious adverse events utilizing the Common Terminology Criteria for Adverse Events (CTCAE) v.5 from study initiation until termination, as well as the Columbia Suicide Severity Rating Scale (C-SSRS). We will also track qualitative data from participant and clinician direct reporting as well as outcomes with the Challenging Experience Questionnaire (ChEQ).

Aim 2 is to assess the efficacy of MBSR+PAP vs. MBSR alone in reducing symptoms of depression, burnout, demoralization, and other clinical symptoms. For continuous outcomes, the analysis will be performed under a generalized linear mixed model (GLMM). The model will include follow-up time as a categorical predictor variable (baseline, 2 weeks, 6 months) as well as the interaction of this categorical factor with the randomized treatment group. Our primary interest lies in the Treatment X Time interaction, expressible as a linear contrast on the β parameters. Repeated effects will incorporate autoregressive dimensioning of the linear predictor, if needed and supported by the Bayesian Information Criterion. In the case that pre-randomization between-groups differences are present in the baseline values of outcome variables, effects will be controlled for chance baseline imbalance using an analysis of covariance strategy that conditions on baseline values. We will use maximum likelihood estimation of missing data for intent-to-treat analyses of all study outcomes.

The statistical model is expressed mathematically as below:

$$Y_{it}=\alpha_{00}+{\alpha_{10}Trt}_{i}+{\alpha_{20}Time1}_{it}+{\alpha_{21}Time2}_{it}+$$

$${\alpha_{30}Trt}_{i}{Time1}_{it}+{\alpha_{31}Trt}_{i}{Time2}_{it}+Z_{i}\beta_{i}+\epsilon_{ijt},$$

$$\beta_{i}\sim N\left( 0, \psi^{2} \right) \left( EQ1 \right)$$

$\epsilon_{it}\sim N\left( 0, \phi^{2}\lambda_{itt} \right), Cov\left( \epsilon_{it}, \epsilon_{it^{'}} \right)=\phi^{2}\lambda_{itt'}$

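### QIDS-SR-16 and the other non-MBI outcome baselines are scheduled after randomisation, and probably after participants know their arm, although the analysis section treats them as pre-randomisation values

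*Protocol*

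**What the plan says.** - **Randomisation.** Table 2 (Protocol section 8) marks "Randomization/assignment | x" in the screening column, days -35 to -7.
- **First outcome scores.** In the same table QIDS-SR-16 is blank in both screening columns and is first marked in week 1 (days 0 to 7). The Demoralization II scale, PCL-5, Watts' Connectedness Scale, TMS/FFMQ-15, trait NADA and Brief Savoring Inventory follow the same pattern. Note v to the table says: "All Questionnaires scheduled for MBSR Week 1 to be administered prior to the first MBSR session".
- **Disclosure.** The trial is open label, and section 9.2 states that "participants will be informed as to study arm assignment prior to the first MBSR session".
- **Arm-specific screening.** Section 10.5: "Laboratory screening will only be required for participants randomized to the MBSR + PAP arm". Table 2 lists these tests in a screening column, and note xi requires the metabolic panel before the MBSR curriculum starts.
- **Ordering around randomisation.** Only one set of measures is expressly ordered this way: "expectancy scales prior to randomization to assess preference as well as post randomization to assess credibility" (section 9.2).
- **MBI.** Section 9.1: "Participants will be administered the MBI-HSS(MP) and the PHQ-9 to evaluate eligibility for participation prior to consent". Table 2 repeats the MBI in week 1.
- **Analysis.** Section 12.2 enters baseline as a level of time and takes the treatment-by-time contrast as the effect of interest. It provides for covariate adjustment "In the case that pre-randomization between-groups differences are present in the baseline values of outcome variables" and describes such differences as due to chance. The Primary Analysis text labels the first QIDS time point as enrollment.

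**The concern.** Randomisation guarantees that the arms are alike in expectation only for what was measured before allocation, or could not be affected by it. A seven-day self-report of mood, completed by someone who already knows whether psilocybin is coming, lacks that guarantee. Relief, hope, apprehension or disappointment could move the score before any treatment is given.

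The efficacy estimate is measured from this value. If the baseline of one arm moves on learning the allocation and then settles, the movement appears in the estimated effect with its sign reversed. Section 12.2's remedy for baseline imbalance assumes that the imbalance arose by chance before randomisation. Conditioning on a baseline that allocation has already influenced reduces this bias but does not in general remove it. An analysis plan cannot supply a pre-randomisation QIDS that was never collected.

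**Working it through.** **1. Order of events.**

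| Event | Where the protocol fixes it | Stated limit |
|---|---|---|
| MBI and PHQ-9 for eligibility | 9.1, Table 2 | before consent, screening |
| Randomisation/assignment | Table 2 | screening, days -35 to -7 |
| PAP-only laboratory tests | 10.5, Table 2, note xi | screening column; before the MBSR curriculum |
| Participant told the arm | 9.2 | before first MBSR session |
| First QIDS and other non-MBI outcome scales | Table 2, note v | week 1; before first MBSR session |

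The schedule itself puts these baselines after randomisation. Their position relative to disclosure is an inference, because both events are bounded only by the first session. The inference is strong. Tests done only in the PAP arm fall before week 1, and expectancy questionnaires, which include a post-randomisation credibility scale, are marked in week 1 alongside QIDS.

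**2. The protocol's own power figure.** Inputs from the Statistical Power text: d = 1.0, alpha 0.05 (taken as two-sided; the protocol does not say), ICC r = 0.5, 12 per arm. Scores are in SD units and the formula is the normal approximation.

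- Baseline-adjusted contrast: variance 1 - r² = 0.75; SE = √(2 × 0.75/12) = 0.354; power = Φ(1/0.354 - 1.96) = 80.7%. This reproduces the stated 81%.
- Simple change to 2 weeks: variance 2(1 - r) = 1; SE = √(2 × 1/12) = 0.408; power = 68.8%. This does not reproduce 81%, which is a separate matter.

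**3. Bias from a reaction at baseline.** Let s be the shift in one arm's baseline mean (SD units) and c the fraction still present at follow-up. Bias is measured against an effect that excludes the reaction itself.

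- Change contrast: s(c - 1)
- Baseline-adjusted contrast: s(c - r) = s(c - 0.5)

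The documents give no value for s or c. With no carry-over (c = 0), no true effect, and type I error = Φ(b/SE - 1.96) + Φ(-b/SE - 1.96) for a bias of size b:

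| s assumed | Change: bias, type I error | Adjusted: bias, type I error |
|---|---|---|
| 0.1 | 0.10, 5.7% | 0.05, 5.2% |
| 0.2 | 0.20, 7.8% | 0.10, 5.9% |
| 0.3 | 0.30, 11.4% | 0.15, 7.1% |
| 0.5 | 0.50, 23.2% | 0.25, 10.9% |

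A simulation with 12 per arm gave 7.5% and 10.9% (change) and 5.7% and 6.9% (adjusted) for s = 0.2 and 0.3, in agreement.

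If d is truly 1.0 and a 0.3 SD shift works against the PAP arm, power falls from 68.8% to 40.3% (change) or from 80.7% to 67.2% (adjusted).

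**4. Dependence on carry-over.** For s = 0.2 to 0.3, signed in the direction of the reaction:

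| c | Change | Adjusted |
|---|---|---|
| 0 | -0.20 to -0.30 | -0.10 to -0.15 |
| 0.5 | -0.10 to -0.15 | 0 |
| 1 | 0 | +0.10 to +0.15 |

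The figures in step 3 are therefore the largest for the change contrast. The adjusted bias vanishes at c = 0.5 and reverses above it.

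**The case against.** The best defence is that no sentence says the questionnaires follow disclosure, and that column position in Table 2 is imperfect evidence of order. The first expectancy mark sits in the second screening sub-column and randomisation in the first, yet section 9.2 wants the preference scale before randomisation. The text also speaks of enrollment and of pre-randomisation values, which may be what was intended. That stands as a caution about disclosure. It does not rescue the schedule: QIDS is blank in both screening columns, and the text and table still disagree.

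Several stronger readings are tempting and should not be drawn.

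- A reader might infer that every outcome lacks a protected baseline. MBI does not: it has a screening score taken before randomisation, although the protocol does not say which MBI score is baseline.
- A reader might assume that one arm is strongly preferred. The protocol measures preference on a two-sided scale with a neutral midpoint and states no result, so the direction of any bias is unknown.
- A reader might conclude that no analysis could help. Allocation is intact, follow-up scores can still be compared between arms, and screening PHQ-9 and MBI are available as pre-randomisation covariates. The limitation belongs to the planned models.

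It is also fair that the adjusted bias of 0.10 to 0.15 SD is small beside a standard error of about 0.35 SD, in a pilot meant mainly to estimate effects and assess feasibility. Nor does moving the baseline remove open-label expectancy: a reaction that persists to follow-up would then remain in the contrast as part of the effect of allocation.

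**Conclusion.** The concern holds in this form: by the protocol's own schedule, QIDS-SR-16 and the other non-MBI outcome baselines are post-randomisation, open-label self-reports, which contradicts the pre-randomisation wording in section 12.2 and does not fit the enrollment label in the Primary Analysis. That they are also post-disclosure is probable but not stated.

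Under an assumed reaction of 0.2 to 0.3 SD in one arm with no carry-over, r = 0.5 and 12 per arm, bias is 0.2 to 0.3 SD for change (type I error about 7.5 to 11%) and 0.10 to 0.15 SD with baseline adjustment (about 6 to 7%). Neither size nor direction can be taken from the documents, and the bias shrinks or, for the adjusted contrast, reverses if the reaction persists. This should be corrected because it touches the primary efficacy outcome and is cheap to avoid. It does not invalidate the randomisation.

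**What to change.** - Collect the existing week-1 outcome questionnaires after consent and before the assignment is generated, or at the latest before it is disclosed, alongside the pre-randomisation preference scale.
- Define those values as baseline in all analyses, and state which MBI score is baseline.
- Keep only the credibility scale after allocation.
- Align Table 2 and note v, section 9.2, section 12.2 and the Primary Analysis text on this order.
- For anyone already randomised without such a baseline, add a sensitivity analysis of follow-up scores adjusted for the pre-randomisation screening PHQ-9 and MBI.

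The cost is a schedule amendment. No assessments are added, and the sample size of 24 and the planned power are unchanged. The downside is that baseline may be up to 35 days before the first session and closer in time to the eligibility scores. This applies equally to both arms, so the between-arm comparison is unaffected in expectation, but within-arm change may contain more regression to the mean.

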## MBSR Arm

Participants randomized to the MBSR only arm will be enrolled in the MBSR curriculum led by [name] LCSW through the University of Utah Resiliency Center. If group size issues arise to complicate feasibility we will incorporate MBSR groups from outside institutions, also paid for by the study. This course is based on the evidence-based model developed by Jon Kabat-Zin at the University of Massachusetts Medical Center. Cost for University of Utah employees ($99) will be covered through the study. Groups meet for an orientation, 9 weekly classes via Zoom of in person (2-2.5 hours each), and an all-day retreat (in person or via Zoom depending on Covid restrictions at the time) held in the final two weeks of the curriculum Guided instruction in various practices is provided, including sitting and walking meditation, body scan, gentle yoga, and mindful communication. These practices are enhanced through inquiry exercises, group dialogue, and daily home assignments. If capacity of internal MBSR courses limit feasibility of the study we will utilize MBSR groups run through Intermountain or Davis Behavioral Health.

<https://app.healthcare.utah.edu/peakCourseRegistration/byCourse;jsessionid=D5D05B9057AA596202DA3A1DD3A81BDE?primaryId=609>

Instruction focuses on three formal techniques: mindfulness meditation, body scanning, and simple yoga postures. Group discussion is a central part of this program, along with regular mindfulness meditation homework assignments which will ideally be practiced daily by participants. Body scanning is the first prolonged formal mindfulness technique taught over the first four weeks of the curriculum. Body Scanning, also known as progressive relaxation, is a type of meditation that utilizes paying close attention to each body part as a way of focusing the mind and becoming more aware of the present moment. Mindfulness meditation is a technique which will build upon this foundation. A technique which has been practiced for thousands of years, participants will focus on different sensations, such as breathing, with a goal to quiet the mind and increase awareness. Basic yoga postures will be used as a stretching practice and a form of moving meditation. MBSR has been validated to help with anxiety and depression (Khoury 2013) and there is reason to suspect it will be helpful with burnout as well.

## MBSR + PAP arm

### MBSR + PAP Preparatory Sessions

Once a subject has completed screening, has been found to be eligible, and has been registered and assigned to the MBSR +PAP arm, Preparatory Sessions may begin with flexible scheduling as indicated in timeline above given scheduling challenges with healthcare providers. See the Schedule of Events and the Assessments Section for treatment period procedures.

The same general themes will be covered during the group Preparatory Sessions.

#### Pre-Psilocybin Session #1:

The group leader will introduce the following topics: establishing safety and boundaries, an introduction of set/setting, an introduction to psilocybin effects, and a discussion of possible difficult experiences including death/transcendence of ego. Participants will be encouraged to remember the following phrases: “Trust/Let Go/Be Open”, “Accept/Be”, and “All is Welcome”

#### Pre-Psilocybin Session #2:

Topics will include a review of psilocybin treatment setting, rules of conduct during psilocybin session including how to handle occasional bathroom/stretching breaks, review of safety guidelines including the rule about no leaving the treatment area, how to handle fear and other challenging emotions, review of rules around physical touch between therapist and participant, review of the use of eyeshades and headphones, and instructions about music.

#### Pre-Psilocybin Session #3.

Topics for Preparatory Session 3 will include a review of the treatment day, the importance of eating a light breakfast, having limited caffeine intake on treatment day, availability of fruit/cheese/crackers later in the treatment day and possibly a light sandwich, the process of monitoring vital signs, the availability of bins for nausea, other unlikely scenarios that might occur including loss of bladder control, fire alarm procedures, and a private room for anyone experiencing emotional distress. A walkthrough of the treatment space will be incorporated.

### MBSR + PAP Psilocybin Session

Each participant will have an individual station in the large group room. They will be provided with eyeshades, blanket, and pillow. They may bring their own token objects of personal significance or meaning that are related to setting an intention for the session.

A brief group meeting will occur starting at approximately 8:00 a.m. The group leader will review the day’s agenda and set the intention for the group. General safety rules and guidelines will be reviewed, as well as procedures for using the restroom.

Participants will then break out with their assigned therapist to set up their station and get ready for medication administration.

Psilocybin will be administered by the group leader at approximately 9:00 a.m. following obtaining a set of baseline vital signs.

A communal music track will be played.

There will be an adjacent individual “break-out” room that a subject plus therapist can move to if there is a perceived need for a period of privacy or a particularly emotionally challenging session that might risk disrupting the group atmosphere for the other participants.

Light snacks and beverages will be available after approximately 1:00 pm.

If a therapist needs a break, the lead therapist will step over to sit with the subject.

At approximately 4:00 pm, the study team will do a brief assessment of each participant to assess whether the medication effect is tapering downward as expected.

At approximately 4:30, participants will complete a short battery of assessments and questionnaires- see Schedule of Events. All participants will have a brief exit assessment by the lead therapist and study team to ensure the patients are safe to go home. This will include evaluation of physical symptoms and functioning, a psychiatric evaluation as to acute suicidality and significant emotional distress, and a cognitive evaluation as to orientation.

Between 5:00-5:30 pm participants, will be allowed to leave with their escorts and return home. They will be instructed to have a quiet evening and a light meal.

An individual therapist as well as the study team will be available by phone for the entire time period between the completion of the psilocybin session and the first integration session.

